### Data management and statistical analysis

A.Sample size selection

Studies of predictive model development indicate that is necessary to include at least 10 events of the dependent variable of interest (in this case: mortality, major complications, relapses or readmissions) for each independent variable included in the multivariate logistic regression model [31, 32]. Therefore, we estimated that at least 100 events of the dependent variable in the sample are required in order to ensure that the regression model would adequately converge. Previous data indicate that the number of events of the dependent variable mortality would be > 15 % of patients operated on in the first year, higher that the expected percentages of other parameters. We therefore estimated that more than 300 events of any of the dependent variables of interest should be included.

Sampling: we consecutively collected all new cases until the sample size was achieved.B.Missing data assumptions and recoding of variables

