Predictive models will be developed to address objectives 1 and 2. The overall sample will be randomly divided into derivation and validation sets. On the one hand, for binary outcomes (such as death, tumor recurrence, major complications, or readmission), multivariate hierarchical logistic models will be used. Goodness-of-fit of models will be assessed by means of the Hosmer–Lemeshow test (*p*-values > 0.05 indicate good model calibration) and the area under the Receiver Operating Curve (ROC), AUC, will be used to evaluate the discrimination ability of the final performance models. An AUC value > 0.80 will indicate that the model discriminates well. Furthermore, multivariate Cox regression models will be used to answer to those objectives. On the other hand, in cases of continuous outcomes (variables related to deterioration of quality of life) as with objective 3, the use of multivariate hierarchical linear mixed models is proposed. The intraclass correlation coefficient (ICC) will be calculated to assess the correlation among observations within a cluster by dividing the patient variance by the total sample variance. A small coefficient would indicate that patients and participant centers are independent.

For study endpoints related to health services research, the following statistical approaches will be used: for two-level outcomes, the Student’s t-distribution or the non-parametric Wilcoxon test (for non-normal distributions) will be applied. Where there are three or more categories in the outcome, ANOVA analysis or a Kruskal–Wallis approach (for non-normal distribution) are the proposed tests. Otherwise, for categorical variables, the Chi-square test (or Fisher’s Exact method, where required) will be used. Multivariate models will be used as needed for appropriate adjustments. For some analyses, subgroups based on tumor location (colon or rectum) will be identified.

An analysis of comparative costs between two alternative surgical approaches (open and laparoscopic surgery) will be performed. For this purpose, generalized linear models (GLM) will be employed using the patient level cost as the dependent variable and taking clinical covariates into account (age, sex, stage, among others). The statistical model will determine which covariates are associated with higher costs, as well as any significant differences in cost between the two alternatives. Analysis will be conducted at 2 and 5 years of follow up.

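### The figure of more than 300 events for any endpoint does not follow from the one rate given, which is that of the commonest endpoint, and it ignores the derivation/validation split

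*Protocol article*

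**What the plan says.** The calculation is in the protocol article, Data management and statistical analysis, part A (Sample size selection). It names four dependent variables: mortality, major complications, relapses and readmissions. The steps are:

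- Each independent variable in the logistic model needs "at least 10 events of the dependent variable of interest".
- From this, "at least 100 events of the dependent variable in the sample are required".
- First-year mortality "would be > 15 % of patients operated on in the first year", which is described as "higher that the expected percentages of other parameters".
- The conclusion is: "We therefore estimated that more than 300 events of any of the dependent variables of interest should be included".

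No rate is given for the other three endpoints. No planned number of patients is given either; the text says only that "we consecutively collected all new cases until the sample size was achieved". The Discussion and Table 1 report 2749 recruited patients.

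Part C (Statistical Analysis) adds a step that part A does not mention. For the predictive models of objectives 1 and 2, "The overall sample will be randomly divided into derivation and validation sets". The shares are not stated. Under Study goals and objectives, objective 1 concerns short-term outcomes and objective 2 mid-term outcomes.

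**The concern.** The conclusion is introduced as a consequence of what precedes it, yet the only rate in the argument is the one declared to be the highest. The highest rate shows what the most frequent endpoint can deliver. It says nothing about the least frequent one.

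Two further gaps point the same way. The events-per-variable rule matters in the data that build the model, and after the split that is only part of the sample. The 15% is also a one-year figure, so it cannot size the short-term models of objective 1.

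At stake is how many predictors each model can carry. A team that takes 300 events per endpoint at face value could consider 300/10 = 30 parameters under the plan's own rule. For a rarer endpoint in a derivation set, the same rule may allow far fewer. The article aims at prediction rules for use in daily practice, so an event count that is too optimistic would raise the risk of overfitted models.

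**Working it through.** **Inputs from the article.** 10 events per variable; minimum 100 events; first-year mortality above 15% (a lower bound); other rates lower, with no figures; recruited N = 2749; random split with no stated share.

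**Assumed here, because the article gives no figure.** Rates of 3% to 12% for rarer endpoints, and derivation shares of 50%, two thirds and 70%.

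**Step 1: can the figure of 300 be reproduced?**

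- Rule alone: 10 events × 10 variables = 100. This gives the minimum, not 300.
- Recruited sample: 0.15 × 2749 = 412. This is consistent with more than 300, but for one-year mortality only.
- Back-solving: 300 / 0.15 = 2000. This matches exactly, but the article never states an N of 2000, and the result again covers mortality only.

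None of these routes gives more than 300 for every endpoint.

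**Step 2: what rate does 300 events need?** Break-even rate = events / N.

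- N = 2749: 300 / 2749 = 10.9%.
- N = 2000: 300 / 2000 = 15%.

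**Step 3: what is left in the derivation set?** Events = N × rate × share, with N = 2749. Only the 15% row uses a rate from the article.

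| Rate | Whole sample | 50% share | Two-thirds share | 70% share |
|---|---|---|---|---|
| 15% | 412 | 206 | 275 | 289 |
| 12% | 330 | 165 | 220 | 231 |
| 10% | 275 | 137 | 183 | 192 |
| 8% | 220 | 110 | 147 | 154 |
| 5% | 137 | 69 | 92 | 96 |
| 3% | 82 | 41 | 55 | 58 |

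At exactly 15%, even mortality stays below 300 in the derivation set. To reach 300 there, the rate would have to be 300 / (2749 × share), which is 21.8%, 16.4% and 15.6% for the three shares.

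**Step 4: when is the 100-event minimum missed in the derivation set?** Rate = 100 / (2749 × share).

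- 50% share: 7.3%.
- Two-thirds share: 5.5%.
- 70% share: 5.2%.

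With N = 2000 the first two thresholds would be 10% and 7.5%.

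**Step 5: what does this mean for model size?** Maximum parameters = derivation events / 10. A 5% endpoint with a 50% share has 69 events, which allows 6 parameters against the 30 that 300 events would suggest. A 10% endpoint with the same share has 137 events and allows 13.

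**The case against.** Several points on the other side are sound.

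- **Lower bound.** Mortality is put above 15%, not at 15%. An endpoint rarer than mortality could still exceed 10.9% and give more than 300 events among 2749 patients. This stands: the figure is unsupported, not shown to be false. In particular, a reader might infer that every endpoint below 15% misses 300. That holds only at N = 2000, which the article does not state.
- **Wording.** If the sentence meant at least one of the endpoints, or if the comparison of rates is a slip, it could be repaired. The natural reading covers each endpoint, and on that reading it does not follow.
- **The minimum refers to the sample.** Part A requires 100 events in the sample, not in the derivation set. Applying the minimum to the derivation set is good practice, but it is a step taken here and not a rule in the article.
- **Later follow-up.** Objective 2 is mid-term, so events can accrue after the first year. This helps those models, but not the short-term ones.
- **Overfitting.** A reader might infer that the models will be overfitted. The article does not fix model size from the 300, and the long list of collected data is not a list of candidate predictors. Only a risk can be claimed.
- **Rectal cancer.** A reader might also infer a worse shortage in separate rectal models. The sentence "For some analyses, subgroups based on tumor location (colon or rectum) will be identified" closes the paragraph on health services endpoints, not the one on prediction models. No separate rectal prediction model is announced for objectives 1 and 2.
- **Level of detail.** A full table of endpoints could be left to an analysis plan. The point here is not missing detail, however. The article draws a numerical conclusion that its premises do not support.

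**Conclusion.** The concern holds in a limited form. The statement of more than 300 events for any dependent variable is not supported by its own inputs. What the inputs support is more than 300 one-year deaths in the full sample: at least 412 among 2749.

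For the other endpoints the shortfall is conditional. It arises against 300 if a rate is below 10.9%. It arises against the 100-event minimum in the derivation set if a rate is below about 7.3% (50% share) or 5.5% (two-thirds share). These thresholds rest on the recruited N and on assumed shares; whether an endpoint falls below them cannot be judged from the article. Separately, the one-year rate gives no basis for the short-term models of objective 1.

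**What to change.** Recruitment is complete, so the change is to the text and to the size of the models:

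1. Withdraw 'any' and limit the figure of more than 300 to one-year mortality in the full sample.
2. State the derivation share. For each endpoint and horizon, restate the expected events in the derivation set, with the rate used.
3. Cap the candidate parameters of each model at derivation events / 10, counted before any selection.
4. Where derivation events are below 100, use a penalised model with a short prespecified predictor list, or label the model exploratory.

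The cost is less favourable stated figures and fewer predictors in some models. No further patients or data collection are needed.

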#### Tumor location

Tumor location was categorized as follows: the appendix, caecum, ascending colon, hepatic flexure and transverse colon were defined as the right colon, whereas the splenic flexure, descending colon, sigmoid and rectosigmoid were defined as the left colon. Rectal tumors were also recorded.

#### Symptomatology

Patient pre-intervention disease-specific symptoms were collected. Where missing observations were observed for any recorded symptom, it was assumed to be asymptomatic. A new variable was created according to the presence/absence of these symptoms to determine whether the patient had experienced any type of symptomatology or not.

#### Complications

A list of several complications (yes/no answers) were collected throughout the course of the follow-up period (intra-surgical, during the hospital admission post-surgical, and at 30 days and 1, 2, 3 and 5 years after the intervention). If missing data were observed for each item in the aforementioned list, no complication was considered to have occurred. Subsequently, at each measurement point, an overall dichotomous variable was defined to classify patients as with and without complications. Complications were also classified into different types, infectious, hematological, surgical or medical.

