**Methods:**

Design: a prospective multicenter cohort study with a follow up period of up to 5 years after surgical intervention. Participant centers: 22 hospitals representing six autonomous communities of Spain. Participants/Study population: Patients diagnosed with colorectal cancer that have undergone surgical intervention and have consented to participate in the study between June 2010 and December 2012. Variables collected include pre-intervention background, sociodemographic parameters, hospital admission records, biological and clinical parameters, treatment information, and outcomes up to 5 years after surgical intervention. Patients completed the following questionnaires prior to surgery and in the follow up period: EuroQol-5D, EORTC QLQ-C30 (The European Organization for Research and Treatment of Cancer quality of life questionnaire) and QLQ-CR29 (module for colorectal cancer), the Duke Functional Social Support Questionnaire, the Hospital Anxiety and Depression Scale, and the Barthel Index. The main endpoints of the study are mortality, tumor recurrence, major complications, readmissions, and changes in health-related quality of life at 30 days and at 1, 2, 3 and 5 years after surgical intervention.

Statistical analysis: In relation to the different endpoints, predictive models will be used by means of multivariate logistic models, Cox or linear mixed-effects regression models. Simulation models for the prediction of discrete events in the long term will also be used, and an economic evaluation of different treatment strategies will be performed through the use of generalized linear models.

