### Follow-up

Follow-up visits up to two years will be performed at all 22 participating hospitals. Due to financial restrictions and organizational resources, 3- and 5-year follow-up visits will be restricted to 18 hospitals (Hospital de Antequera, Hospital Costa del Sol, Hospital Universitario de Valme, Hospital Universitario Virgen del Rocío, Hospital Universitario Virgen de las Nieves, Hospital Universitario de Canarias, Corporació Sanitaria Parc Taulí, Hospital del Mar, Hospital Clínico San Carlos, Hospital Universitario La Paz, Hospital Infanta Sofía, Hospital Universitario Fundación Alcorcón, Hospital Galdakao-Usansolo, Hospital Universitario Araba, Hospital Universitario Basurto, Hospital Universitario Cruces, Hospital Hospitalario Donostia, and Hospital Universitario Doctor Peset).

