### Anticipated issues

The main limitations of this type of study design are those related to missing patients as a result of an extensive follow-up period (5 years, in this instance) and, at the same time, missing data related to some variables, especially those related to patient questionnaires. To minimize these risks, all patients are informed of the objectives of the study prior to enrollment and again during the follow-up visits. Furthermore, to reduce missing data from questionnaires, up to three letters are sent to patients and conversion to phone visits is available upon request. Given the lengthy follow up period, regular patient contact are established. Furthermore, the contact physicians at each hospital remind patients of their participation in the study where possible.

An additional issue is the reliability of data gathering by reviewers. To standardize the collection of data and avoid errors, all reviewers are adequately trained and have received specific instructions on how to collect data for each variable.

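### Missing complication items become no complication at every time point, with no exception for time points never assessed, so patients who died, were lost or were not visited can count as event-free

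*Protocol article*

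**What the plan says.** The Complications paragraph, under the missing-data and recoding part of the protocol article, covers a list of yes/no items collected during surgery, "during the hospital admission post-surgical, and at 30 days and 1, 2, 3 and 5 years after the intervention". Its missing-data rule is: "If missing data were observed for each item in the aforementioned list, no complication was considered to have occurred". The next step is that "at each measurement point, an overall dichotomous variable was defined to classify patients as with and without complications". That variable has two classes and none for a time point that was not assessed.

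Four other places bear on how often a time point will be blank, and on what the variable is used for:

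- Follow-up: "3- and 5-year follow-up visits will be restricted to 18 hospitals", out of 22 that recruited.
- Study design: follow-up ends at 5 years or at death. The sample size paragraph expects more than 15% of patients to die in the first year.
- Anticipated issues: a main limitation is "missing patients as a result of an extensive follow-up period".
- Abstract and Statistical Analysis: "The main endpoints of the study are mortality, tumor recurrence, major complications, readmissions" and changes in quality of life; and "for binary outcomes (such as death, tumor recurrence, major complications, or readmission), multivariate hierarchical logistic models will be used". Cox models are planned as well.

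The pTNM staging paragraph treats absence differently. If neither the pathological nor the clinical stage is available, stage stays missing.

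**The concern.** A blank item can mean two things: the record was reviewed and nothing was found, or there was no patient, no visit and no review. The rule gives both the same code. Its wording could mean that any blank item is set to no, or that a patient with all items blank is classed as having none. Under either reading, a patient with no data at a time point enters as without complications.

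If such patients stay in the analysis, two things follow. The complication rate falls, because people who could not have been observed with an event are counted in the denominator. The model coefficients also shift, because being unassessed is not random: it follows death, and at years 3 and 5 it follows hospital. A factor that predicts death removes patients from observation and files them as event-free, so it is pushed towards looking protective against complications. The planned random split into derivation and validation sets would not show this, since both parts carry the same coding. The intended product is a set of prediction rules for clinicians, so a shifted coefficient would be carried into use.

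**Working it through.** **1. Reproduce the denominator.** The area totals in Table 1 sum to 490 + 101 + 689 + 343 + 998 + 128 = 2749, and the 22 hospital counts give the same figure. This matches the stated total.

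**2. Hospitals without 3- and 5-year visits.** The 18 hospitals listed under Follow-up were compared with the 22 listed under Study design. Missing are Althaia (100 patients in Table 1), Bidasoa (33), Mendaro (28) and Zumarraga (39). 100 + 33 + 28 + 39 = 200; 200/2749 = 7.3%. The largest possible denominator at 3 and 5 years is 2749 − 200 = 2549.

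**3. Deaths.** The sample size paragraph gives first-year mortality above 15%. Using 15% as a floor, 0.15 × 2749 ≈ 412 patients cannot be assessed for the interval from year 1 to year 2.

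**4. Patients coded event-free without assessment, if all 2749 are kept.** The article gives no loss rate, so loss among survivors is an assumption, shown from 0 to 20%. Assessable at years 3 and 5 = 2549 × 0.85 × (1 − loss). Apparent rate = true rate × assessable/2749, with an assumed true rate of 20% among assessable patients.

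| Assumed loss | Assessable | Coded no without assessment | Apparent rate (true 20%) |
|---|---|---|---|
| 0% | 2167 | 582 (21.2%) | 15.8% |
| 5% | 2058 | 691 (25.1%) | 15.0% |
| 10% | 1950 | 799 (29.1%) | 14.2% |
| 20% | 1733 | 1016 (36.9%) | 12.6% |

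With the four hospitals alone, and no deaths or losses, 20% becomes 0.20 × 2549/2749 = 18.5%. At year 2, with the 15% death floor and no loss, it becomes 0.20 × 0.85 = 17.0%. Deaths after year 1 are not counted here and would lower these rates further.

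**5. Effect on an odds ratio.** Suppose a risk factor changes mortality before the interval, and the dead are coded no. Coded rate = true rate × (1 − mortality). All rates in this step are assumed.

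- Complication rate 20% in both groups (true odds ratio 1.00), mortality 10% versus 30%: coded rates are 0.20 × 0.90 = 0.18 and 0.20 × 0.70 = 0.14. Odds ratio = (0.14/0.86)/(0.18/0.82) = 0.74.
- The same with mortality 10% versus 20%: coded rates 0.18 and 0.16, odds ratio 0.87.
- Complication rate 20% versus 30% (true odds ratio 1.71), mortality 10% versus 30%: coded rates 0.18 and 0.21, odds ratio 1.21.
- The same with mortality 10% versus 20%: coded rates 0.18 and 0.24, odds ratio 1.44.

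In each case the estimate is lower than the true value. How much lower depends on the assumed mortality difference.

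**The case against.** The strongest reply is that the rule concerns items, not who is analysed. The article does not define the denominator at any time point, and it does not say that the dead, or patients of the four hospitals, stay in the 3- and 5-year analyses. This stands. A reader might infer that the 200 patients are certain to be coded event-free, that four hospitals will show a rate of exactly zero and that the hospital effect will be distorted. The article does not support that as a certainty; it follows only if the rule is applied to the whole cohort. What remains is that the rule is stated without a limit and nothing else in the article supplies one.

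Second, complications come from medical records, read by trained reviewers with a form and a manual. In a completed review, an unmarked item can fairly mean that none occurred, and an unreturned questionnaire does not blank the record. This also stands, so there is no case here for imputing unmarked items in a reviewed record. It does not cover an interval that nobody reviewed.

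Third, the hospital argument has limited reach. All 22 hospitals have visits up to two years, and the Background gives 1 or 2 years as examples of the medium term. The 200 patients therefore matter only for the 3- and 5-year analyses.

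Fourth, death is an endpoint in its own right, and Cox models can censor at death. True, but the two-class variable and the logistic models are still planned as described.

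Fifth, the recoded variable is any complication, while the main endpoint is major complications, and degree of complication is recorded separately. The link between them is implied, not stated.

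Finally, the baseline symptom variable follows a similar rule: "Where missing observations were observed for any recorded symptom, it was assumed to be asymptomatic". A reader might take it as the same fault. Death, loss and dropped visits cannot explain a blank baseline symptom, so it is a separate and weaker matter and does not support this point.

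**Conclusion.** The point holds as a fault in a stated rule. As written, the coding does not separate nothing found from not assessed, and no exception is given for death, loss or hospitals without visits. Applied to the whole cohort, it lowers the complication rate and pushes predictors of death towards looking protective.

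The only exact figure for size is the count of patients in hospitals without 3- and 5-year visits: 200 of 2749 (7.3%). With the 15% first-year mortality floor, about 582 (21.2%) would be unassessed at those visits before any loss. The apparent rates and the odds ratio of 0.74 rest on assumed complication, mortality and loss rates; they show direction and plausible scale and are not estimates for this cohort. The conclusion also assumes that unassessed patients are kept in the denominator, which the article neither states nor excludes, and that major complications are derived from the same items. The death and loss part can affect years 1 and 2 as well as later years.

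**What to change.** - Code an unmarked complication item as no only when the medical record for that interval was reviewed and the patient was alive and under follow-up at the start of the interval. Otherwise set it to missing or not at risk.
- Take patients who died before the interval out of its denominator. Take the four hospitals out of the denominators at years 3 and 5.
- State the resulting denominator for each time point.
- Report the coding of unassessed time points as no complication only as a sensitivity analysis.

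Death is already recorded at each stage of data collection, and the hospitals with late visits are known. The article does not say whether completion of the record review was logged for each patient and interval; if it was not, that has to be reconstructed. Beyond this recoding, the cost is fewer analysable patients and slightly wider intervals. If the analyses were always meant to be limited to assessed patients at risk, stating that limit next to the rule is enough.
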